## Abstract

**Background:**

Chronic obstructive pulmonary disease (COPD) is the most common chronic lung disease creating an immense burden on social health care systems. Pulmonary rehabilitation (PR) has proven to be effective in patients with COPD. However, exercise training as the basis of PR becomes extremely tedious, occasionally causing a loss of perseverance in patients. Therefore, we considered an approach that makes this technique interesting and easier to persist. The aim of this project was to explore an exercise training approach based on PR-integrated coached exercise training to promote the new exercise training approach as a form of group rehabilitation activity in the future.

**Methods:**

Participants will be randomly divided into the trial and control groups. The trial group will be treated with PR-integrated coached exercise training (plus usual care). All exercise programs will be guided by sports coaches with a physical education background. Meanwhile, the control group will receive traditional PR and home exercises, including walking and swimming. The study will last for 12 weeks. The primary outcome measure is exercise tolerance using the 6-min walking test and secondary outcomes are the peak oxygen uptake of cardiopulmonary exercise tests, the COPD Assessment Test, and the St. Georges Respiratory Questionnaire. Other evaluated outcomes include changes in postbronchodilator forced expiratory volume at 1^st^ second, forced vital capacity, body fat and muscle composition, and mental status measured using the Hamilton Anxiety and Depression Scales.

**Discussion:**

This study provides a simple, feasible, repeatable, and fun exercise training approach. To the best of our knowledge, there are no randomized controlled trials in the existing literature on PR-integrated coached exercise. The protocol shared in our study can be used as a reference for exercise training in patients with COPD.

**Trial registration:**

Ethical approval (BF2020-236–02) was obtained from the Guangdong Provincial Hospital of Chinese Medicine Human Research Ethics Committee. All participants signed an informed consent form. ChiCTR-2100043543. The registration date is 2021/02/21 and it is the third version.

**Supplementary Information:**

The online version contains supplementary material available at 10.1186/s13063-022-07058-2.

## Introduction

Chronic obstructive pulmonary disease (COPD) is a common, preventable, and treatable disease, characterized by persistent respiratory symptoms and airflow limitation. Airway obstruction leads to continual dyspnea, cough, sputum production, and systemic effects [1]. In 2010, the global prevalence of COPD was estimated at 11.7%, with an overall increasing trend [2]. According to the World Health Organization, COPD will become the fifth largest disease burden and the third largest cause of death by 2020 [3–5].

Pulmonary rehabilitation (PR) has been shown to be an effective therapeutic strategy to improve shortness of breath, health status, and exercise tolerance in COPD and is an important part of integrated patient management [6]. Supervised maintenance exercise training at least twice a week forms the foundation of PR and encompasses endurance training, interval training, resistance or strength training, flexibility, and inspiratory muscle training. All interventions are aimed at maximizing personal functional gains [7]. Due to individual differences, development of a uniform exercise training program becomes impossible. Walking is the most common form of training and is recommended at a constant speed of 80–120 steps per min, at least 45 min each time, to achieve a heart rate in the target range and maintain it for more than 10 min [8]. The cycle ergometer is a frequent choice for endurance training.

Available evidence indicates that optimum benefits are achieved from programs lasting for 6–8 weeks [7]. However, there are numerous challenges faced along the way and exercise training occasionally becomes too monotonous to sustain for some patients. When the program is unsupervised, patients fail to effectively carry on with the exercise training. Walking exercises without supervision cannot achieve the targeted intensity [9]. Additionally, only a minority of patients favor cycling. A study in China showed that only 3.8% of 80 patients approved of cycling [10].

Over the past few years, efforts have been made to provide more integrated, patient-centered PR programs, and engagement in sports has been suggested as a convenient setting for health promotion [11]. There are sports clubs that organize and provide opportunities for competition and participation in community sports. And also, researchers found that PR program supplemented with virtual reality techniques is beneficial intervention to improve physical fitness in patients with COPD [12]. In China, traditional Chinese medicine exercises such as Baduanjin and Tai Chi are popular and are proved to be effective exercise training [13, 14].

The integration of medicine into sports training was first proposed in physical education to prevent diseases [15]. Sports coaches focus on helping patients by conducting exercise training in an effective and interesting manner. Therefore, PR-integrated with coached exercise training may be a viable approach that offers a patient-tailored, individualized intervention, targeting long-term adherence to health-enhancing behaviors.

Considering the role of a sports coach in maintaining the efficiency and persistence of exercise training, we invited a sports coach to the PR team and designed a randomized, controlled clinical trial. The aim of the project was to explore an exercise training pattern based on PR integrated with coached exercise training.

## Methods and analysis

### Study setting

This study is a prospective, parallel-group randomized, controlled, exploratory clinical trial. Participants will be recruited from the Guangdong Provincial Hospital of Chinese Medicine Clinic. They are outpatients attending a clinic or inpatients being discharged home and evaluated by two experienced respiratory physicians. Patients are invited to meet with the research physicians to discuss any remaining questions and sign the informed consent. Thereafter, the participants are randomly assigned to either the trial or control group as a ratio of 1:1. The trial group will receive PR integrated with coached exercise training. The control group will receive a traditional PR program. Owing to the exercise intervention, it is not possible to blind participants or those involved in the provision of care. However, the researchers collecting primary data and performing statistical analyses will be blinded to the allocation. The design is open label with only outcome assessors and data analysts being blinded, so unblinding will not occur. The study design is shown in Fig. 1.

**Fig. 1 Fig1:**
[figure not shown]
Flow chart describing study design

### Eligibility criteria

We will include participants aged between 40 and 80 years, diagnosed with COPD (a post-bronchodilator FEV1 < 70% and < 80% of predicted normal values), who are clinically stable, have not experienced an acute exacerbation for at least 4 weeks before the trial, do not participate in systematic exercise training in the past 6 months, and have a 6-min walk test (6MWT) distance between 350 and 550 m.

We will exclude participants with severe comorbidities, including coronary heart disease, arterial aneurysm, severe hepatic and renal dysfunction, and uncontrolled hypertension. Patients with mental diseases, deafness, limb activity disorder, and inability to cooperate are also excluded from the trial.

Patients can leave the study at any time for any reason. Intervention can also be ended by the investigators if the patient is uncooperative and does not attend study visits. This study will be ended in case of any abundance in adverse events or procedure-related complications.

### Randomization

A list of random numbers is generated using IBM SPSS statistical software (version 23.0). Hence, every participant will match a number and the information is blind to other trialists. Opaque envelopes containing a number are used to randomly assign participants to either the trial or control group. Two trialists will generate the allocation sequence and assign participants to interventions together.

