### Adverse event reporting

Adverse events will be recorded in CRF (Case Report Form). Serious adverse events will be reported within 24 h to the principal investigation and Institutional Review Board. The steering committee consists of a pulmonologist and a respiratory nurse who will survey the study procedure and evaluate serious adverse events. The steering group is the trialists of this study. If there is any damage related to the study, the research group will pay the medical expenses and make corresponding financial compensation according to laws and regulations.

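### The two trialists who generate the allocation sequence also assign participants, so the opaque envelopes do not secure concealment against them

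*Protocol article*

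**What the plan says.** The Randomization section describes four elements. A random-number list is produced in SPSS. Each participant is matched to a number, with the knowledge restricted as follows: "every participant will match a number and the information is blind to other trialists". The concealment device is: "Opaque envelopes containing a number are used to randomly assign participants to either the trial or control group". The division of labour is: "Two trialists will generate the allocation sequence and assign participants to interventions together".

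Other sections give the setting. Under Study setting, patients are "evaluated by two experienced respiratory physicians", then meet research physicians and consent, and only afterwards are "randomly assigned to either the trial or control group as a ratio of 1:1". The same section states: "The design is open label with only outcome assessors and data analysts being blinded". The Interventions section places randomization after the baseline data are collected. The Adverse event reporting section describes the steering committee as a pulmonologist and a respiratory nurse, and adds: "The steering group is the trialists of this study".

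**The concern.** Concealment requires that whoever controls a patient's entry or assignment cannot find out the next arm. The usual way to achieve this is to keep generation of the list apart from its use. Here the article gives both tasks to the same two people, acting together.

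At stake is the comparability of the arms at entry. Participants and care providers know the arm, and the primary outcome is a walking test that depends on effort. If someone with access to the sequence can choose when, or in what order, patients are assigned, fitter or more motivated patients could end up preferentially in one arm. Blinding outcome assessors and analysts protects measurement and analysis. It does nothing about selection at entry.

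**Working it through.** The point is procedural and rests on no figure, so the check sets the statements side by side.

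1. **Who makes the sequence?** Two trialists (Randomization).
2. **Who assigns?** The same two, together (same sentence).
3. **Who is kept from the information?** The other trialists (Randomization). On its natural reading, this leaves the two as the exception.
4. **What is the safeguard?** Opaque envelopes containing a number. An envelope protects against someone who has not seen the list. It does not protect against the person who produced it.
5. **Does any other section separate the tasks?** No. Study setting, Interventions, Adverse event reporting and Data management name no independent or central party that generates or holds the list.
6. **Do the two also screen or enrol?** Not stated. Study setting mentions two respiratory physicians and research physicians, and nothing identifies them with the two trialists. Adverse event reporting equates the trialists with a steering group made up of a pulmonologist and a respiratory nurse, which suggests clinical staff. That sentence cannot be a full roster: if the trialists were only those two, there would be no others to keep blind. It is an indication of overlap, not proof.
7. **When does assignment happen?** After consent (Study setting) and after baseline measurement (Interventions). This order is sound. It does mean that a patient's baseline results may already be known when someone with access to the sequence handles the assignment.

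From items 1 to 5, those who assign have access to the sequence, and no stated safeguard stops them from using it. Items 6 and 7 bear on how much harm could follow. They do not change that conclusion.

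**The case against.** The strongest reply is that no route to steering is shown. Patients are evaluated and consented by physicians who may be among those kept blind. The two assigners would then receive people who are already eligible, consented and measured. If so, the exposure is smaller. This stands as a limit on the consequences. It does not secure concealment, because the two would still control the order and timing of assignment and nothing in the text rules out that they also enrol.

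A second reply is that a journal article condenses the full protocol, and that sealing and sequential numbering of envelopes are details it may leave out. That is right, and the absence of those words is not held against the plan. The point rests on what the article states about roles. Further detail on the envelopes would not by itself separate them.

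Three stronger readings are tempting, and the document does not support them:

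- **That the two actually know each upcoming arm, or hold the list at assignment.** The text says that they generate the sequence. It does not say who keeps the list afterwards or how a number is turned into an arm. Access follows from the text; actual foreknowledge is an inference.
- **That a definite shift in baseline walking distance would pass into the result.** Any such shift would be hypothetical. Baseline distance is measured, so an imbalance in it would largely cancel with change scores or baseline adjustment. The article specifies a t-test at the end of the trial without saying whether final values or changes are compared.
- **That the bias could not be removed in the analysis at all.** This is true only of selection on unmeasured traits.

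**Conclusion.** The point holds in this form: one pair of people both generates the sequence and assigns from it, so concealment against that pair is not secured. This is a procedure the article states, not a detail it omits, and it bears on the primary comparison.

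The size of any resulting bias cannot be computed from the document. A reader might infer that allocation was in fact foreseen or manipulated; nothing in the text shows that. The conclusion assumes only that people who generate a sequence have access to it. How serious the consequence is depends on a fact the article does not give: whether either of the two takes part in screening or enrolment. If they do, patients could be selected at entry. If they do not, the exposure is confined to the timing and order of assignment.

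**What to change.** Separate the roles within the existing team and replace the sentence on the two trialists accordingly:

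- One person with no part in screening, enrolment, assignment or treatment generates the list, prepares sealed, sequentially numbered opaque envelopes, and keeps the list inaccessible to the others.
- A different person opens the next envelope, and only after the patient's identifier has been recorded on it.
- The existing order, with consent and baseline measurement before assignment, is kept.

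The cost is a change of wording and a reassignment of duties. If both of the present trialists have clinical duties in the trial, the list should pass to another team member who has none of the excluded roles.

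The change cannot repair allocations already made. Participant timeline and Trial status put the start of recruitment in March 2021, and Trial status plans it to run through November 2023, so only patients still to be randomized are protected. For those already randomized, the sponsor should document who generated the list, who had access to it, and whether those people took part in screening or enrolment.

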### Sample size calculation

For the primary outcome, a change of 25 m in the 6-MWT distance is considered to be the minimal important difference (MID) in patients with COPD [16], based on a two-sample independent *t*-test with a given MID of 25 m, standard deviation of 44.6 m, power of 80%, and significance level of 0.05 [17]. Accordingly, the calculated sample size of each group is 50. Assuming a dropout rate of 15% resulted in 18 patients being included in the final study population.

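### The stated study population of 18 contradicts the calculated 50 per group with 15% dropout, which gives about 118 in total; taken literally, 18 leaves about 20% power instead of 80%

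*Protocol article*

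**What the plan says.** The Sample size calculation section of the protocol article starts from the primary outcome: "a change of 25 m in the 6-MWT distance is considered to be the minimal important difference (MID) in patients with COPD". The calculation is "based on a two-sample independent" t-test with "standard deviation of 44.6 m, power of 80%, and significance level of 0.05". From these inputs it concludes: "Accordingly, the calculated sample size of each group is 50". The next sentence then gives the size of the trial: "Assuming a dropout rate of 15% resulted in 18 patients being included in the final study population".

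The Study setting section fixes equal allocation: "the participants are randomly assigned to either the trial or control group as a ratio of 1:1". The Data management and statistical analysis section says that incomplete data from patients lost to follow-up will be discarded, so dropouts reduce the number analysed. No other section of the article text gives a total or per-group recruitment target.

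**The concern.** Two consecutive sentences give sizes that cannot both describe the same trial. Fifty per group is 100 patients before any allowance for dropout. The allowance should take the number above 100, yet the printed result is 18.

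The recruitment target tells the trial team when enrolment is complete, and it is the figure against which achieved enrolment is later judged. As the sentence stands, a report of 100 or 118 patients would look like a large departure from plan. A report of 18 would look compliant while having little chance of detecting the trial's own 25 m difference.

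**Working it through.** **Inputs** (Sample size calculation, except allocation, which is in Study setting): difference 25 m; SD 44.6 m; power 80%; significance level 0.05; 1:1 allocation; dropout 15%. Sidedness is not stated. I take two-sided, because only that reproduces the stated 50 (one-sided gives 40 or 41).

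**Step 1: reproduce the 50 per group.**

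Normal approximation: n = 2 × (1.960 + 0.842)² × (44.6/25)² = 49.96, so **50 per group**. The stated figure reproduces.

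By the noncentral t distribution, which matches the test named, n = 50.94, so 51 per group. Power at 50 per group is 79.3%; at 51 it is 80.0%.

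**Step 2: apply the 15% dropout.**

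| Route | Calculation | Result |
|---|---|---|
| Inflate per group | 50/(1 − 0.15) = 58.8 | 59 per group, **118 in total** |
| Inflate the total | 100/(1 − 0.15) = 117.6 | 118 in total |
| Multiplicative shortcut, total | 100 × 1.15 | 115 in total |
| Multiplicative shortcut, per group | 50 × 1.15 = 57.5 | 58 per group, 116 in total |
| Attrition from 100 | 100 × 0.85 | 85 remaining |
| From 51 per group | 51/0.85 = 60 | 60 per group, 120 in total |

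No route gives a study population of 18. Two simple slips would produce the digit pair: 118 with its first digit lost, or the patients added for dropout, 118 − 100 = 18 (equivalently 118 × 0.15 = 17.7 expected dropouts).

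**Step 3: what 18 would mean if taken literally** (25 m, SD 44.6 m, two-sided 0.05):

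| Reading of 18 | Evaluable per group | Power, noncentral t | Power, normal approximation |
|---|---|---|---|
| 18 in total | 9 | 20.1% | 22.0% |
| 18 in total, then 15% lost | 7.65 | 17.5% | 19.4% |
| 18 per group | 18 | 37.2% | 39.0% |

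With 9 per group, 80% power requires a true difference of 62.7 m, which is 62.7/25 = 2.5 times the stated minimal important difference. Alternatively, the SD would have to be about 17.8 m rather than 44.6 m. With 18 per group the detectable difference is 42.9 m.

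**The case against.** The strongest reply is that this is a reporting slip and not a trial planned at 20% power. The intended design is stated one sentence earlier. A recruitment window from March 2021 to November 2023 sits poorly with a target of 18, and both likely explanations lead back to 118. The flow chart (Fig. 1) and the SPIRIT checklist are not visible here, nor is the registry record, and any of them may carry the right number. This largely stands. The power loss is therefore conditional on the literal reading, and it cannot be claimed that the ethics committee or the trial team is working to 18. It does not remove the error: the article calls itself the definitive protocol version, describes the trial as exploratory (so a small sample cannot be ruled out on sight), and its text offers nothing that settles the number.

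Three narrower objections also have some force:

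- The 17.5% figure may count dropout twice if 18 is meant as the number left after dropout. That is why 20% is the main figure.
- The inflation formula is not stated, so 118 is the best-supported total rather than the only possible one; the shortcut gives 115 or 116.
- The gap between 50 and 51 per group is 0.7 percentage points of power and is immaterial on its own. The finding does not rest on it.

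**Conclusion.** The sentence is wrong as written and must be corrected. The derivation of 50 per group is sound (49.96 by normal approximation), but a population of 18 does not follow from 50 per group and 15% dropout under any inflation or attrition formula. The consistent target is 118 in total, 59 per group.

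If 18 were the actual total, power for 25 m would be about 20% rather than 80%, and 37% if it meant 18 per group. No reading of 18 as a population comes near the stated power. These figures assume a two-sided 0.05 level, an SD of 44.6 m and equal allocation. That 18 is a slip for 118, or for the number added for dropout, is an inference that the sponsor has to confirm.

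**What to change.** Replace the last sentence of the Sample size calculation section with wording such as:

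> Fifty evaluable patients per group are required (79% power by two-sided t-test at the 0.05 level). Allowing for 15% dropout, 59 patients per group, 118 in total, will be randomised.

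If a full 80% by t-test is wanted, state 51 evaluable and 60 randomised per group (120 in total). If 18 really is the planned total, keep it but restate the power for a 25 m difference as about 20%.

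Then confirm that the same target appears in the flow chart, the registry and the ethics file. The cost is one corrected sentence and a consistency check; no trial procedure changes.

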### Interventions

After baseline data collection, the patients will be randomly divided into the trial or control group. Participants in both the groups will receive usual care, and PR included health education, nutrition guidance, psychological support, and exercise training [6, 18]. The intervention will be performed three times per week for 12 consecutive weeks. The only difference in intervention between both groups is the exercise training.

In the control group, exercise sessions, which mostly included walking and swimming, lasted for at least 30 min, three times a week, with a weekly follow-up. In contrast, patients in the trial group will receive exercise training guided by a sports coach, which lasts for 60 min, once a week at the hospital, and for 30 min, twice a week at home, conducted through a video. Exercise training for the trial group consists of warm-up exercise, aerobic exercise, resistance exercise, respiratory rhythm adjustment, and respiratory muscle training.

